### Design

A randomized Controlled trial will be conducted to examine whether FG-cs are effective in changing: (1) child’s safety (i.e., decrease in (risk for) abuse/neglect; less supervision orders or shorter supervision order; less or shorter out of home placement); (2) the involvement of the broader social network; (3) perceived control over the problems in the families, empowerment of parents; improvement of family functioning; (4) less use of professional care. A second aim is to study whether the effectiveness of FG-c is influenced by characteristics of the implementation of the methodology, characteristics of the family managers (such as education, or attitude towards FG-c), or by family characteristics (such as size of the social network, ethnicity or family type: single/married).

Using computerized randomization two comparable groups will be formed. Until the inclusion of 300 families is completed (presumably within 6 months), every family starting care at Youth Care Agency Amsterdam (YCAA) will be randomly allocated to care with or without a Family Group conference. Because allocation to care with a FG-c will not always result in an actual Family Group conference and/or an approved Family Group plan, 200 families will be assigned to care with FG-c and 100 families to care without FG-c. Five multi-informant/source (parent, family manager; FG-coordinator; member of the family’s social network; child (if > 8 years of age), and file analysis) assessments will be carried out in both groups. Pre-tests will take place before FG-cs starts. Subsequently, in both groups post-tests will be carried out 1, 3, 6 and 12 months after the FG-c has taken place (see also Figure 1 for the flow chart).

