### Study sample

We aim to include *N* = 300 families, who will be randomized in a 2 (FG-c): 1 (control group) ratio to ensure that there is enough power to also conduct the planned moderator analyses. These groups are large enough to detect effects of FG-c’s.

Given the goal of YCAA to carry out 800 FG-c’s each year, the inclusion of 300 families will be completed within six months. This sample size is sufficient to test the hypotheses with an alpha of .05 and a small to medium effect (*d* = .35). FG-c can be used for all families, so there are no exclusion criteria in this study.

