### Instruments

An overview of the concepts, instruments and sources of information is presented in Table 1. At the 5 assessment points, the family manager, a member of the network, parent, the family group coordinator and the child (if older than 8 years) will be asked to answer questions, either online, or by telephone. The families and child will receive assistance when filling out the questionnaires.

**Table 1 T1:** Concepts, instruments and informants at the different assessment points

	**Domain/concept**	**Instrument**	**Test**					**Source**					
			**T1**	**T2**	**T3**	**T4**	**T5**	**FM**	**MN**	**P**	**FGC**	**R**	**C**
Primary outcome													
	Safety	LIRIK	x		x	x	x	x	x				
		Safety line	x	x	x	x	x	x					
		CAPI	x		x		x	x	x	x			
		Succint		x		x	x	x	x	x			
Secondary outcomes													
	Commitment	PSQ	x	x	x	x	x	x		x			
		ISEL	x	x^1^	x^1^	x	x	x					
		Succint	x	x^1^	x^1^	x	x	x		x			
	Control/empowerment	Interview	x	x	x	x	x	x	x	x			
		Succint	x	x	x	x	x	x					
		FES	x	x^1^	x^1^	x	x	x					
	Family functioning	PSI	x^1^	x^1^	x^1^	x^1^	x^1^		x				
		Succint	x	x	x	x	x	x					
		FES	x	x^1^	x^1^	x	x	x					
	Family functioning	PSI	x^1^	x^1^	x^1^	x^1^	x^1^			x			
	Professional care	File research	x	x	x	x	x					x	
Cost- effectiveness	Costs	Cost questionnaire	x			x	x			x			
Moderators													
Characteristics implementation FG-c and family manager	Number of families	Registration form	x	x	x	x	x					x	
	Role FM	Registration form		x	x	x	x	x	x	x	x	x	
	Chacareristics FM	Registration form	x									x	
	Time to FG-c	File analysis	x	x								x	
	Number members network at FG-c	Registration form		x							x	x	
	Phases FG-c/plan carried out as intended	Registration form	x	x	x	x		x			x	x	
Characteristics families	Demograpgics	File research/questionnaire	x	x	x	x	x	x		x		x	
	Risk factors	Risk factors List	x					x		x		x	
	Problems child	BPC (if child > 8)	x			x	x						x

*Note*: T1 = pretest (questionnaire); T2 = post-test after 1 month (interview by telephone); T3 = post-test after 3 months (interview by telephone); T4 = post-test after 6 months (questionnaire); T5 = follow-up assessment after 12 months (questionnaire); FM = Family Manager; MN = member network; P = Parent; FG-c = Family Group-conference; FGC = Family Group Coordinator; R = researcher; C = Child; ^1^ = selection of the original instrument.

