### Primary outcomes

The primary outcome is child safety. This outcome will be assessed by using various child safety indicators. First, to measure whether the safety in families has increased the Light Instrument to assess Risk of Child Abuse (Lirik) [21] will be used at all assessment points. This instrument is filled out by the Family manager. The Lirik is widely used in the Netherlands and is a standard procedure for the YCAA family managers.

Additionally, after each case management meeting, family managers fill out the ‘safety line’ of the family. Families are given a safety score between 1 and 10. This is a new measurement method, used by YCAA as standard practice. These multiple assessment points allow to detect changes in safety over time.

Furthermore, parents will be asked to fill out the Child Abuse Potential Inventory short version (CAPI) [22]. This is a widely used instrument to identify child abuse potential [23]. A Dutch version has been translated and validated by Grietens, De Haene, and Uyttebroek [24].

The “Success of Intervention Inventory”(Succint) will be used to evaluate the success of the intervention (care with or without FG-c). This questionnaire measures whether changes are visible in safety, perceived control and social support/cohesion. The Succint has been developed by PiResearch, especially to evaluate the success of FG-c [8]. This instrument will be filled out by a parent, family member, and family manager.

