### Statistical analyses

Missing data will be imputed so that all participants will be included in the analyses, and using LISREL 8.8, the multiple imputation will be carried out by the expectation maximization algorithm [37]. Both an intention to treat as well as a completer analysis will be performed.

In order to examine the effectiveness of FG-c overall effectiveness will be examined for all outcome measures by conducting an ANCOVA, with the outcome measures at post-test as dependent variables, treatment condition as factor and pre-intervention scores of the outcome variables as co-variates, as is recommended for RCTs using pre- and post-tests [38]. Effect sizes will be computed as Cohen’s d, based on adjusted means and standard errors.

For categorical moderator analyses, the same ANCOVA’s will be conducted, with the moderators as factor. Post-hoc analyses for moderator effects will be conducted by splitting the file according to the moderator and again conducting an ANCOVA and calculating effect sizes separately for each group. Regression analyses will be conducted for the continuous moderators.

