Additionally, a rich set of instruments will be used, so that if there is any effect on any of the outcomes, there is a large likelihood to identify this effect. Moreover, potential moderators in terms of program as well as participant characteristics will be examined, so that the present study will provide information on when and for whom FG-cs are most likely to be effective. Program integrity will be examined and fulfillment of each phase of FG-c will be registered. Finally, the cost-effectiveness of FG-c will be examined: valuable information for both politicians as well as families who invest time in a FG-c.

However, there are also several limitations, which may threaten the value of our study. First, there is a risk in having this many informants and assessment moments (5 time points). There is the risk that the families or other informants will drop out of the study. We will put a lot of effort in maintaining the families in the study. Thankfully, the research group has experience with motivating for and retaining participants in research [39], but this always needs full attention.

Additionally, TAU in the control group may cause smaller effect sizes when compared to no treatment in the control group. However, as the research question is whether FG-c adds something to the usual child care services, this is the most logical design.

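### Child safety is declared the one primary outcome but defined as four unranked instruments with several informants and post-tests, so no single primary test exists and false-positive risk is uncontrolled

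*Protocol article*

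**What the plan says.** Primary outcomes declares a single outcome: "The primary outcome is child safety". It continues: "This outcome will be assessed by using various child safety indicators". Four instruments follow: LIRIK, the safety line, CAPI and Succint. None is ranked above the others and no composite is defined.

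The same section names the family manager for LIRIK and the safety line, and the parent for CAPI. For Succint, "This instrument will be filled out by a parent, family member, and family manager".

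Table 1 under Instruments ("Concepts, instruments and informants at the different assessment points") gives the times. Under Design, "in both groups post-tests will be carried out 1, 3, 6 and 12 months after the FG-c has taken place".

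Under Statistical analyses, "overall effectiveness will be examined for all outcome measures by conducting an ANCOVA". The dependent variable is the post-test score and the covariate is the pre-intervention score; which of the four post-tests is meant is not said.

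Under Study sample: "This sample size is sufficient to test the hypotheses with an alpha of .05 and a small to medium effect", d = .35. The Discussion lists breadth of measurement among the strengths: "a rich set of instruments will be used, so that if there is any effect on any of the outcomes", the chance of finding it is large.

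**The concern.** A primary outcome should lead to one identifiable test, or to a stated rule for combining several. Here the article fixes a concept and an unranked set of measures. Any significant instrument, informant or time point could then be reported as better child safety. If informants or time points disagree, the protocol gives no way to decide what the trial found.

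This matters because the article says its results should inform policy and public spending on conferences, and because it cites controlled studies pointing to possible harm. The d = .35 sample-size statement also cannot be tied to a particular endpoint.

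**Working it through.** **1. The plan's own figure.** Inputs from Design and Study sample: 200 versus 100 families, d = .35, alpha .05. Two-sided testing and 80% power are assumptions, since the article states neither.

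- Control-group size = (1 + 1/2) × (1.960 + 0.842)² / 0.35² = 96.1, so 97; total 3 × 97 = 291, close to 300.
- Standard error of d = √(1/200 + 1/100) = 0.1225; 0.35 / 0.1225 = 2.858; power = Φ(2.858 − 1.960) = 81.5%.

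At 85% or 90% power the total would be 330 or 387, so 300 fits one two-sided test at about 80% power. With Bonferroni over four instruments (.05/4 = .0125, critical value 2.498), power per test is Φ(2.858 − 2.498) = 64%, and 80% power would need 411 families.

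**2. Counting the safety tests** (informants from Primary outcomes, post-test times from Table 1).

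| Instrument | Informants | Post-tests | Tests |
|---|---|---|---|
| LIRIK | family manager | T3, T4, T5 | 3 |
| Safety line | family manager | T2 to T5 | 4 |
| CAPI | parent | T3, T5 | 2 |
| Succint | parent, family member, family manager | T2, T4, T5 | 9 |
| Total | | | 18 |

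Without Succint, 9 remain. The text has LIRIK at every assessment, which would add T2 and make 19. Taking the source columns of Table 1 literally (LIRIK 3 × 2, safety line 4 × 1, CAPI 2 × 3, Succint 3 × 3) gives 25, but those columns conflict with the text and are not used as the lead. The count leaves out supervision orders and out-of-home placement, which Design also places under child safety, and the second analysis set (completers).

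**3. Chance of at least one false significant result.** For m independent tests this is 1 − 0.95^m in either direction and 1 − 0.975^m in the favourable direction. For m = 18: 1 − 0.95¹⁸ = 0.603 and 1 − 0.975¹⁸ = 0.366. Correlated cases use equally correlated normal test statistics, by numerical integration. The article gives no correlations, so 0, 0.5 and 0.7 are assumptions.

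| Tests | Either direction, r = 0 / 0.5 / 0.7 | False improvement, r = 0 / 0.5 / 0.7 |
|---|---|---|
| 1 | 5% | 2.5% |
| 4 (one per instrument, one time) | 19 / 16 / 13% | 10 / 8 / 6.5% |
| 9 (without Succint) | 37 / 27 / 20% | 20 / 13 / 10% |
| 18 | 60 / 40 / 28% | 37 / 20 / 14% |

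At a correlation of 0.8, 18 tests still give 22% in either direction and 11% for false improvement.

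**4. Table 1 against the text.**

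- LIRIK: the text has every assessment and the family manager; Table 1 omits T2 and adds the network member.
- CAPI: the text has parents; Table 1 marks three sources.
- Succint: the safety row has no T1 mark, yet the stated ANCOVA adjusts for the pre-intervention score. Other Table 1 rows do schedule Succint at T1.

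**The case against.** The strongest defence is that this is a condensed article, and that multiplicity adjustment and testing order are commonly left to an analysis plan. That stands: the absence of an adjustment is not the finding. What the article does itself is define the primary outcome as an unranked set, and the choice of primary measure and time point belongs in the protocol.

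Second, the article never says that every informant and time point will be tested separately at .05. The .05 appears only in the sample-size text, which speaks of hypotheses in the plural, and no rule is given for declaring safety improved. This also stands, so the 18-test and 9-test figures are conditional. The Discussion sentence about any effect on any outcome is a remark on sensitivity, not a decision rule.

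A reader might go further than the documents allow in three ways.

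- **25 tests and a 72% risk of falsely claiming improvement.** The 25 rests on Table 1 source columns that contradict the text. The 72% (25 independent tests) counts harm as well as benefit.
- **The Succint analysis is impossible, so the instrument must be dropped.** The questionnaire is scheduled at T1 in other rows, so the missing mark may be a slip in the table. It needs reconciling.
- **Succint is disqualified because it was developed to evaluate conferences.** That is not in itself an error.

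**Conclusion.** The concern holds in this form: the article declares one primary outcome but no primary test, while its sample size fits a single two-sided .05 test.

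The size depends on how the analysis is carried out. If informants and post-tests are tested separately at .05, the chance of a false improvement in child safety is 14% to 37% over 18 tests, or 10% to 20% without Succint, against 2.5% for one test. With one test per instrument at one time it is 6.5% to 10%. These ranges assume correlations from 0.7 down to 0, and that any one significant safety measure could support the claim; the article neither states nor excludes that. The lack of a designated test does not depend on any of these assumptions.

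**What to change.** Before outcome data are examined:

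1. Designate one primary test at two-sided .05: one instrument or a pre-specified composite, one informant and one time point, using a measure with a T1 value. Parent-reported CAPI at 12 months is one example; the choice is the investigators'.
2. Make the other safety measures secondary or supportive.
3. Tie the d = .35 sample-size statement to the designated test and state the power.
4. Reconcile the Table 1 informants and times for LIRIK and CAPI with Primary outcomes, and the missing T1 mark in the Succint safety row with the baseline-adjusted ANCOVA.

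The cost is small. Data collection need not change, the error rate stays at 5%, and power at 300 families stays at 81.5% under the inputs above. The other safety measures lose primary status, and the registry entry may need updating.

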### Secondary outcomes

In order to assess the commitment of the *social network,* The Parenting Support Questionnaire (PSQ) [25] will be used to assess perceived support of the social network. Additionally, social support concerning well-being and housing will be assessed with the Interpersonal support evaluation questionnaire - short (ISEL) [26]. Additionally, the changes in social support will also be addressed with the Succint questionnaire [8].

The *perceived control* will be assessed with an interview concerning perceived control by the researcher. Parent, EK-coordinator, Family manager and a member of the network will be interviewed. Additionally, Perceived control will be assessed with the Succint [8]. Finally, empowerment of the parents will be assessed with the Family Empowerment Scale (FES) [27].

The *quality of family functioning* will be assessed with the Parenting Stress Index Short form [28]. This instrument assesses parental stress in child rearing situations. Additionally, family functioning in terms of problem definition and reason to search help is registered with the FG-checklist, an instrument standard used in the FG working procedure. Additionally, the Family Assessment Device (FAD) [29], consisting of 12 items, will be used to assess quality of family functioning. Moreover, file analysis will be used to identify family functioning issues.

Finally, Basic Needs Satisfaction in General Scale (BNSG-S) will be used to assess ’satisfaction of basic psychological needs’ [30]. This questionnaire consists of three subscales: autonomy, competence and social connectedness. This instrument is translated to Dutch [31] and validated for a mentally delayed population. Additionally, the Satisfaction with Life scale [32], consisting of 5 items, is used to assess general well-being of parents.

Finally, the use of professional care will be retrieved from files at each of the 5 assessment points. Trained coders will code the use of professional care.

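### ANCOVA and Cohen's d are fixed for every outcome, including event, count and duration outcomes; at 200:100 the pooled standard errors are biased when FG-c changes the rate or duration

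*Protocol article*

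**What the plan says.** The Statistical analyses section prescribes a single model: "overall effectiveness will be examined for all outcome measures by conducting an ANCOVA". The post-test value is the dependent variable, with "treatment condition as factor and pre-intervention scores of the outcome variables as co-variates". One effect measure follows: "Effect sizes will be computed as Cohen’s d, based on adjusted means and standard errors". No other model is named for the overall comparison of the arms.

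Not all the outcomes named elsewhere are scale scores. The Design section spells out child safety, the primary outcome, as including "less supervision orders or shorter supervision order; less or shorter out of home placement"; the Background gives the same definition. Use of professional care is a secondary outcome: "the use of professional care will be retrieved from files at each of the 5 assessment points", and "Trained coders will code the use of professional care". Table 1 gives care use its own row, with file research at all five time points.

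Allocation is unequal: "200 families will be assigned to care with FG-c and 100 families to care without FG-c".

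**The concern.** The article is not silent here in a way that a separate analysis plan would be expected to fill. It states a rule for all outcomes, and the rule suits questionnaire scores better than events, counts or durations.

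For an event the variance is tied to the mean, and for time in placement it usually is too. A treatment effect on such an outcome therefore makes the arm variances unequal. ANCOVA pools them, and with twice as many families in one arm the pooled estimate is weighted towards that arm. The standard error is then too small if the smaller (control) arm has the larger variance, and too large in the opposite case.

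The direction matters. An apparent benefit of FG-c on placements would look more precise than it is, and an apparent harm less precise. The Background cites a systematic review of controlled studies that found more and longer placements and more care use after FG-c, so harm is a live possibility for these outcomes. Separately, a standardised mean difference for a yes/no order or for mostly-zero placement days tells a policy maker little.

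**Working it through.** **The plan's own figure.** Study sample calls 300 families at 2:1 sufficient for d = 0.35 at alpha .05; power and sidedness are not stated. Assuming 80% power and a two-sided test, the control arm needs (1 + 1/2) × (1.960 + 0.842)² / 0.35² = 96.1, so 97. The total is 97 + 194 = 291. Power at 200:100 is 0.815 (0.813 by the noncentral t). The statement reproduces under those assumptions, for an outcome with equal arm variances.

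**Inputs.** n₁ = 200 (FG-c) and n₀ = 100 (control) come from Design. One residual variance follows from ANCOVA. The document gives no event rates or durations, so all of those below are assumptions.

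**Formulas for a yes/no outcome.** Variances are v = p(1 − p).
- Pooled SE² = [(199v₁ + 99v₀)/298] × (1/200 + 1/100)
- True SE² = v₁/200 + v₀/100
- Coverage = 2Φ(1.96 × pooled SE / true SE) − 1

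**Example, 5% (FG-c) vs 15% (control).** v₁ = .0475 and v₀ = .1275. The pooled variance is (9.4525 + 12.6225)/298 = .07408, so the pooled SE is √(.07408 × .015) = .0333. The true SE is √(.0002375 + .001275) = .0389. The ratio is .857 and coverage is 90.7%.

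| FG-c vs control | Pooled/true SE | Coverage (formula) | Coverage (simulated ANCOVA) |
|---|---|---|---|
| 15% vs 15% | 1.00 | 95.0% | 95.7% |
| 20% vs 30% | .956 | 93.9% | – |
| 10% vs 15% | .944 | 93.6% | – |
| 10% vs 20% | .910 | 92.6% | 92.6% |
| 5% vs 15% | .857 | 90.7% | 90.3% |
| 30% vs 20% | 1.046 | 96.0% | – |
| 15% vs 10% | 1.059 | 96.2% | – |
| 20% vs 10% | 1.098 | 96.9% | 96.7% |
| 15% vs 5% | 1.167 | 97.8% | 97.7% |

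The simulations used 8,000 runs with a baseline covariate in the model.

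**Placement days.** These were simulated as zero unless placed, with exponential durations if placed, at 200:100.

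| Placed, FG-c vs control | Mean days if placed | ANCOVA coverage | With robust (HC3) SE |
|---|---|---|---|
| 15% vs 15% | 120 vs 120 | 95.2% | 94.2% |
| 10% vs 20% | 120 vs 120 | 92.2% | 93.7% |
| 10% vs 20% | 90 vs 120 | 89.1% | 92.8% |
| 20% vs 10% | 120 vs 120 | 96.9% | 95.1% |

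**Is unequal allocation the cause?** With equal arms the pooled and true SE for a difference in proportions coincide. At 150:150 the simulated cases, binary and duration, give 94.1–95.4%.

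**Do robust standard errors help?** At 200:100 they bring the simulated binary cases to 94.6–95.5%. Durations improve only partly, with 92.8% the worst case.

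**Power to detect harm, 15% vs 5%.** The pooled SE is √(.10092 × .015) = .0389; the true SE is √(.0006375 + .000475) = .0334. With correct SEs, z = .10/.0334 = 3.00 and power is Φ(3.00 − 1.96), about 85%. With the pooled SE, the estimate must exceed 1.96 × .0389 = .0763, so power is Φ[(.10 − .0763)/.0334], about 76%.

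**Cohen's d.** The same 10-point difference gives .10/√.07408 = .37 when FG-c has 5% and control 15%, but .10/√.10092 = .31 when the rates are reversed. The measure depends on the direction of the effect.

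**The case against.** The strongest reply is about scope. Supervision orders and placements appear only in definitions of child safety, in the Background and Design. Primary outcomes lists LIRIK, the safety line, CAPI and Succint as the indicators, and Table 1 has no row for orders or placements. The ANCOVA wording, with its pre-intervention scores, fits those instruments. This stands as a limit: that orders and placements will go through ANCOVA is implied, not stated. Care use is different, since it is an explicit secondary outcome with its own row. Its scale is not given, however, and every family is entering youth care, so many zeros cannot be taken for granted there.

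The second reply is about size. The rates are assumed, and for yes/no outcomes with smaller contrasts, such as 10% vs 15% or 20% vs 30%, coverage misses by only 1–2 points. That also stands.

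Three stronger readings are tempting, and the document supports none of them:
- **The intervals are wrong in general.** They are about right when the arms do not differ, so type I error is roughly kept. The article also promises no confidence intervals, although its tests and effect sizes rest on the same standard errors.
- **The method hides harm.** In the 15% vs 5% case the pooled z is still .10/.0389 = 2.57, and the expected interval, about 2.4 to 17.6 points, excludes zero. The loss is one of power.
- **There is no baseline to adjust for.** For care use a T1 value is planned. For orders and placements the document says nothing either way.

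**Conclusion.** The point holds in a limited form. A stated rule applies one pooled-variance model and one standardised effect size to all outcomes. It fits badly any that are events, counts or durations: care use if coded that way, and orders and placements if analysed. At 200:100 the standard errors are sound when the arms do not differ and biased when FG-c changes the rate or duration. With assumed occurrence of 5–30% and mean placement of 90–120 days, coverage is about 89–94% if FG-c lowers the rate and 96–98% if it raises it. The lower end needs a large contrast or a shift in both occurrence and duration. The difficulty of interpreting Cohen's d for yes/no or zero-heavy outcomes does not depend on any assumed rate.

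**What to change.** Restrict ANCOVA and Cohen's d to scale scores. For yes/no outcomes, such as any supervision order or any placement, report a risk difference or ratio from logistic regression, modified Poisson regression, or a linear model with robust standard errors. For days or care contacts, report mean differences with robust or bootstrap intervals. Robust errors alone did not fully restore coverage for skewed days, and the bootstrap was not tested here, so the choice deserves a short simulation once rates are known. Keep the T1 value as a covariate wherever it is collected, as it is for care use. The wording should also say whether orders and placements are analysed as outcomes.

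The cost is a change in analysis wording and slightly more analysis work in standard software. No new data are needed, and allocation and sample size stay as they are.

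### The moderator analysis names no condition-by-moderator interaction; read literally, it tests prognosis and subgroup-by-subgroup significance, not whether the FG-c effect differs between families

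*Protocol article*

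**What the plan says.** The opening of Methods and design makes moderation the second of two main research questions. Under Design the article writes "A second aim is to study whether the effectiveness of FG-c is influenced by characteristics of the implementation of the methodology"; the same sentence goes on to family-manager characteristics and to family characteristics such as network size, ethnicity and family type. The Discussion promises that "the present study will provide information on when and for whom FG-cs are most likely to be effective".

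The method is given in three sentences of Statistical analyses:

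- **Categorical moderators.** The main ANCOVA (condition as factor, pre-test score as covariate) is repeated "with the moderators as factor. Post-hoc analyses for moderator effects will be conducted by splitting the file according to the moderator", with an ANCOVA and an effect size calculated in each part of the file.
- **Follow-up.** The split is called post-hoc, but no condition for carrying it out is stated.
- **Continuous moderators.** "Regression analyses will be conducted for the continuous moderators". No model is given.

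On size, Study sample presents the 2:1 allocation as a "ratio to ensure that there is enough power to also conduct the planned moderator analyses", and the Discussion lists a sample large enough for moderators among the study's strengths.

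**The concern.** The null hypothesis of the second question is that the FG-c minus usual-care difference is the same at every level of the moderator. Neither of the steps named tests it.

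- The test of a moderator entered as a factor has the null that adjusted post-test means are equal across its levels. That is prognosis. Risk factors and family type could well predict child safety in both arms whether or not FG-c does anything.
- Each split-file ANCOVA has the null of no FG-c effect in that subgroup. Finding one subgroup significant and the other not does not show that the two effects differ.

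The stake is the advice on which families to offer FG-c. The Background says moderators are useful for engaging those most likely to benefit and for adjusting the program. A prognostic factor or a chance disagreement between two subgroup tests could be turned into such advice.

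**Working it through.** **Inputs from the article.** N = 300, as "200 families will be assigned to care with FG-c and 100 families to care without FG-c" (Design); alpha .05 and d = .35 (Study sample). No power figure, sidedness or interaction effect size is stated.

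**Assumptions.** Two-sided test; residual SD √(1−r²) in units of the outcome SD, with pre-post correlation r = 0 or .5; a binary moderator splitting families 50/50 or 70/30, with 80/20 as an extreme; a prognostic effect of .35 or .20 SD; no true moderation. Power is Φ(effect/SE − 1.96).

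**1. The plan's own figure.** Control n = (1.96 + 0.84)² × (1 + 1/2) / 0.35² = 96.1, so 97, and 3 × 97 = 291 in total. With 100 and 200 families, SE = √(1/100 + 1/200) = 0.1225 and power is 81.5%. The 300 is therefore consistent with 80% two-sided power for the **main effect**.

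**2. Moderator entered as a factor, no interaction.** SE = √(1−r²) × √(1/n₁ + 1/n₂), where n₁ and n₂ are the moderator groups.

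| Split | r | SE | Significant at .35 SD | Significant at .20 SD |
|---|---|---|---|---|
| 50/50 | 0 | 0.115 | 86% | 41% |
| 50/50 | .5 | 0.100 | 94% | 52% |
| 70/30 | 0 | 0.126 | 79% | 36% |
| 70/30 | .5 | 0.109 | 89% | 45% |

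Simulation (4,000 trials per setting) gives 78-94% at .35 SD and 34-51% at .20 SD. With no prognostic effect the rate is 5%.

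**3. Split file with the same d = .35 in everyone.** With subgroup powers p₁ and p₂, the chance that exactly one is significant is p₁(1−p₂) + p₂(1−p₁).

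- 50/50, r = 0: each half has 50 control and 100 FG-c families, SE = √(1/50 + 1/100) = 0.173, power 52.4%. Discordance = 2 × .524 × .476 = 50%.
- 50/50, r = .5: power 64.6% in each half; discordance 46%.
- 70/30, r = 0: power 66.7% and 34.7%; discordance 55%.
- 70/30, r = .5: power 78.8% and 43.9%; discordance 53-54%.

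Across simulations the range is 44-56%. Equal halves already disagree in roughly half of trials, so unequal subgroup size is not needed. At 80/20 the figure rises to 61-64%.

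**4. Interaction test under the same conditions.** Simulated rejection is 4-6%. If the file is split only after a significant interaction, a false discordant pair occurs in about 4-5% of trials (simulated at r = .5).

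**5. What the interaction test can detect at N = 300.** SE = √(1−r²) × √(sum of 1/n over the four condition-by-moderator cells).

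| Split | Power for a .35 SD interaction, r = 0 / .5 | Detectable at 80% power, r = 0 / .5 |
|---|---|---|
| 50/50 | 30% / 38% | .69 / .59 SD |
| 70/30 | 26% / 33% | .75 / .65 SD |
| 80/20 | 21% / 26% | .86 / .74 SD |

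**The case against.** The strongest reply is that the article omits the interaction without excluding it. The ANCOVA to be repeated already holds condition as a factor, so adding the moderator makes a two-factor model, which is often fitted with its interaction. Calling the subgroup analyses post-hoc fits a simple-effects follow-up to a significant interaction, and then the false discordance rate is only about 4-5%. Term-by-term detail is also commonly left to a full plan, and the sentence on continuous moderators states no model that could be wrong. Finally, effect sizes per subgroup are legitimate description, and nowhere do the authors say they will infer moderation by comparing subgroup p-values.

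Much of this stands. A reader might infer that the plan rejects an interaction term, or that the trial will report false moderators. The document supports neither. The rates above hold only on the literal reading, and the factor-test rates also require that the characteristic is prognostic and that its main effect is taken as moderation.

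It does not dispose of the point. The article does more than leave detail open: it prescribes a procedure for a main research question, and the split-file step carries no stated condition. A full plan that followed the wording would inherit the fault. For continuous moderators, a product term has to be specified deliberately.

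**Conclusion.** The point holds as a fault of specification. As written, the procedure names no test of the trial's second main question, and one natural reading has error rates far above the nominal 5%: 78-94% for a purely prognostic characteristic at .35 SD (34-51% at .20 SD), and 44-56% for disagreement between two subgroups under a uniform d = .35. These figures rest on the literal reading and on the assumed correlations, splits and prognostic effects, none of which the article gives.

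The primary comparison of FG-c with usual care is unaffected. The point covers baseline characteristics measured in both arms, such as family type, ethnicity and risk factors. Variables that exist only in the FG-c arm, such as network members attending the conference or time to its start, have no estimable interaction with condition and fall outside it. Family-manager attitude belongs here only if recorded at baseline in both arms: Design lists it as a manager characteristic, while Moderators records support for FG-c under the manager's role in carrying it out.

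**What to change.** Replace the moderator sentences in Statistical analyses with wording such as: *For each baseline moderator measured in both arms, the model contains condition, moderator, condition × moderator (a product term for continuous moderators) and the pre-test score. Moderation is judged only by the interaction, reported as the difference in FG-c effects (for continuous moderators, the change in effect per unit) with its 95% CI. Subgroup effect sizes with CIs are estimated from the same model and are descriptive. Separate subgroup p-values are not used to claim that FG-c works in one group and not in another.*

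Restate the claims in Study sample and Discussion that the sample suffices for moderator analyses. The stated calculation supports d = .35 for the main effect only; an interaction must be about .59 to .86 SD to be detected with 80% power.

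The cost is a few sentences and one model term, with no new data. The real downside is that fewer moderators will reach significance, because power for a .35 SD interaction is only about 21-38%.
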